#### Secondary analysis

All secondary study parameters will be assessed with descriptive analysis, with formal tests merely serving to gain an estimation of possible group differences. Group differences will all be represented by point estimates and 95% confidence intervals. Within-group changes (pre–post, T_0_–T_1_) in motivation for taking part in the intervention (on the SMFL) and in mental health status (HADS-D) will also be tested formally with a mixed-effects model to estimate a time × group interaction effect and individual differences. Additionally, usability (SUS) and user satisfaction (CSQ-I) scores will be compared with the established benchmarks. Mood as measured by the smartphone records, and scheduled and recorded activities as measured in the platform, will only be analyzed descriptively. No subgroup analyses will be performed.

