### Assessments

Assessments will be taken after enrollment (T−1), at baseline (T_0_), and at the end of study participation 4 weeks after baseline (T_1_). Questionnaires will be self-administered and completed online. Table 1 provides an overview of the measures employed at specific time points.

**Table 1 Tab1:** Measures administered at each assessment interval

Questionnaire	Aim	Enrollment (T−1)	Allocation (T_0_)	Post-study (T_1_)
Mental health				
PHQ-9	*Screener*	X		
HADS-D	*Mental health*		X	X
Feasibility				
SUS	*System usability*			X
CSQ-I	*User satisfaction*			X
Study completion	*Reasons for non-adherence*			X
Motivation				
SMFL	*Current use*		X	X
Continued use	*Continued use*			X
Coach acceptance				
WAI-SR*	*Relationship*			X
Acceptance*	*Acceptance*			X

*Applies to the intervention group only

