### Randomization and blinding

Participants will be randomly assigned by an independent researcher to either Moodbuster Lite with automated support (intervention group) or Moodbuster Lite without automated support (control group). That will take place in a 1:1 ratio and on the basis of a computer-generated block randomization table with random block sizes [25]. Group allocation cannot be blinded to participants, because a description of the study’s research aim—improving intervention adherence with automated support by a virtual coach—must be provided in the information letter; whether or not automated feedback is provided will hence be obvious to participants. The principal investigator, who coordinates the study and conducts the data analysis, will not be blinded to the participants’ group allocation.

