### Secondary outcome measures

#### Motivation

Motivation for taking part in the intervention will be assessed in both groups by the Short Motivation Feedback List (SMFL) [39]. It consists of eight 10-point Likert-scale items ranging from “completely disagree” to “completely agree,” designed to capture the level and type (external, introjected, or identified) of a patient’s treatment motivation. The SMFL is based on self-determination theory [40] and has been found to have a congeneric reliability ranging from 0.81 to 0.93 [39]. There are two different versions. The pre-intervention version will be assessed at baseline (T_0_) and the post-intervention version after 4 weeks (T_1_). Motivation to continue using the intervention will be assessed by a single statement, “I intend to continue using the platform to schedule and perform activities,” assessed on a 5-point Likert scale ranging from “completely disagree” to “completely agree.”

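### SMFL and HADS-D: the planned time × group contrast is unbiased but less precise than a baseline-adjusted T1 comparison, and within-group SMFL change spans two versions not stated to be comparable

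*Protocol article*

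**What the plan says.** Under Secondary analysis, the protocol article treats secondary parameters as descriptive, with formal tests serving only to estimate possible group differences. It then singles out two outcomes, the SMFL and the HADS-D. For each, the change inside an arm from T0 to T1 is the stated object, and the article says that it "will also be tested formally with a mixed-effects model to estimate a time × group interaction effect and individual differences". The object of that sentence is change within each arm; the quantity it names is a contrast between arms. It does not specify the random effects, say whether the arms share a baseline mean, or mention a T1 comparison adjusted for T0.

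Table 1 gives each of these outcomes at T0 and T1 only. Under Motivation the article says of the SMFL: "There are two different versions. The pre-intervention version will be assessed at baseline", with the post-intervention version following at T1. It does not say how the versions differ or whether their scores are comparable. For the HADS-D it describes one instrument for both times.

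The Assessments text calls T0 baseline, while Table 1 heads the same column "Allocation (T_0"). Under Randomization and blinding, participants are not blinded: "whether or not automated feedback is provided will hence be obvious to participants".

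**The concern.** Two separate matters arise.

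The first is precision. Baseline scores are already collected for both outcomes. A time × group interaction with unconstrained baseline means subtracts the whole T0 score, whatever its correlation with T1, whereas adjustment subtracts only the part that predicts T1. A pilot of 70 that reports point estimates with 95% intervals would carry wider intervals than its own data require.

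The second is meaning. If the SMFL versions differ in content or scale, the within-arm difference between T0 and T1 combines a change of questionnaire with any change in motivation. The Background names within-group as well as between-group motivation as a secondary aim, and treats motivation as part of the route from the coach to adherence, so a within-arm SMFL test is likely to be read as substantive.

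**Working it through.** The plan has no figure of its own on this point. N = 70 (35 + 35) follows a cited pilot recommendation; no effect size, SD, power or T0–T1 correlation is given, so there is nothing to reproduce.

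**Inputs.** From the article: two time points, 1:1 allocation, 35 per arm. Assumed: correlation rho from 0.3 to 0.9, equal T0 and T1 variances (SD = 1), complete data, two-sided alpha 0.05.

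**1. What the interaction estimates.** In one simulated complete dataset of 70, a random-intercept time × group model gave 0.6845 (SE 0.2715). A simple comparison of change scores gave the same estimate and SE. ANCOVA on the same data gave SE 0.236.

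**2. Precision.** SE(change) = √(2(1−rho)) × √(2/35). SE(adjusted) = √(1−rho²) × √(2/35). √(2/35) = 0.239. The variance ratio is (1−rho²)/(2(1−rho)) = (1+rho)/2.

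| rho | SE change | SE adjusted | Variance ratio | Equivalent gain in N (1/ratio − 1) |
|---|---|---|---|---|
| 0.3 | 0.283 | 0.228 | 0.65 | 54% |
| 0.5 | 0.239 | 0.207 | 0.75 | 33% |
| 0.7 | 0.185 | 0.171 | 0.85 | 18% |
| 0.9 | 0.107 | 0.104 | 0.95 | 5% |

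For an assumed true difference of 0.5 SD, power under change and adjusted analysis respectively is 42% and 59% (rho 0.3), 55% and 68% (rho 0.5), and 77% and 83% (rho 0.7).

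**3. Effect of two SMFL versions** (4,000 simulated trials per scenario, rho 0.5, 35 per arm).

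- No true effect, and the T1 version reads 0.5 SD higher in both arms: the apparent control-arm change is 0.51 SD, although nothing changed. The interaction averages −0.005 with 5.9% rejection; the adjusted contrast averages −0.003 with 5.5% rejection. The shift damages the within-arm result and cancels between arms.
- The T1 version also has 0.7 times the scale: with no true effect both contrasts stay centred on zero (rejection 5.4% and 5.6%). With a true effect of 0.5 SD, power is 37% for change and 66% for the adjusted contrast.

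The shift and scale values are illustrations, not estimates of how the versions differ.

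**4. Individual differences.** One score at each of two times gives a 2 × 2 covariance matrix with 3 distinct elements. A random intercept plus residual has 2 parameters and is identified. Adding a random slope and its covariance with the intercept makes 4 parameters against 3 elements, so individual change could not be separated from error.

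**5. Timing of T0.** If knowing the allocation shifted T0 by an assumed 0.3 SD and there were no T1 effect, the change contrast would be biased by −0.30 and the adjusted one by −rho × 0.3 = −0.15 at rho 0.5. The simulation gave −0.304 and −0.152. Adjustment is less affected but not immune.

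**The case against.** The case for the plan as written runs as follows.

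- *The group contrast is valid.* This stands. A reader might infer from the two SMFL versions that the time × group result is biased; the documents do not support that, because randomisation makes a common version shift cancel. For the HADS-D the instrument does not change, and efficiency is the only issue.
- *No random slope is planned.* This also stands. A reader might take the phrase on individual differences to mean individual differences in change, and expect a model that cannot be fitted. The article names no slope, and a random intercept satisfies the wording. The two-time-point limit is a reason to state the intercept explicitly, not evidence of a faulty model.
- *The versions may differ trivially.* Possibly. The difference is described only in a cited source that is not at hand, so it cannot be called material. But the article plans a formal test of change across the versions without saying that they are comparable, and that gap remains.
- *The precision argument is a preference on descriptive outcomes.* In part. The gain depends on an unknown correlation and shrinks to 5% of variance at 0.9. A mixed model with a common baseline mean would recover about the same precision, and the article does not exclude one. Still, adjustment has the lower variance at every rho below 1 under the stated assumptions and needs no new data.

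**Conclusion.** The point holds in a limited form. The planned interaction is unbiased; if baseline means are unconstrained, it gives up 5% to 35% of variance relative to a baseline-adjusted T1 comparison over assumed correlations of 0.9 down to 0.3, with equal variances and complete data. Within-group SMFL change cannot be interpreted as change in motivation while the comparability of the two versions is unstated.

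The impact is modest. These outcomes are secondary and mainly descriptive, and N = 70 does not rest on them. A reader might also infer that the primary adherence model should be adjusted for baseline SMFL; nothing here bears on that analysis. The advantage of adjustment further assumes that T0 is completed before participants know their allocation, which the Table 1 heading leaves open.

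**What to change.** Reword the Secondary analysis section as follows:

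- For SMFL and HADS-D, estimate the group difference at T1 adjusted for the T0 score, with its 95% interval. Use ANCOVA, or a two-time-point model with a common baseline mean and unstructured covariance, which also keeps participants who lack T1. The pre-intervention SMFL enters as a covariate only.
- Report SMFL at T0 and T1 descriptively, as separate versions, without a within-group change test unless the versions are shown to be comparable.
- State that any modelling of individual differences is limited to a random intercept.
- State that T0 is completed before allocation is known, and align the Table 1 heading with the text. If T0 comes later, say so, because both the adjustment and the common baseline mean then need defending.

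The first three changes cost wording only, since both baseline scores are already planned. The fourth is also wording if T0 already precedes knowledge of allocation; otherwise it means changing the order of two steps.

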#### Data management

On the informed consent form, participants will be asked if they agree to the use of their data in future research on the same topic at VU University, and to their data being shared with regulatory authorities when required. This trial does not involve the collection of biological specimens for storage. All raw data will be stored on a secure local server at the VU University in Amsterdam, which is regularly backed up. Paper-based documents will be stored in a keycard-secured archive at the Department of Clinical, Neuro- and Developmental Psychology. All participants will be de-identified upon randomization by linking their participant number to a random study participant code. In the study, participants will be referred to exclusively by that participant code, and the document linking the two numbers will be destroyed once the study is over and results have been disseminated. Because this study is relatively small and investigator-initiated, no data monitoring committee or auditing process is required. Because we do not expect serious negative outcomes for the participants, we do not conduct an interim analysis and there are no subsequent formal stopping rules.

## Discussion

The study described in this protocol paper is a pilot randomized controlled trial that will compare an unguided intervention for low mood with the same intervention with additional automated guidance provided in the form of a virtual coach. The main goal is to gain an estimate of the effectiveness of the virtual coach in terms of improving adherence to the intervention. That will help determine the feasibility and necessity of a future larger-scale trial.

Many studies have shown that online interventions that include human guidance are generally more effective than ones that do not. Human therapists or coaches that can provide such guidance are not always available, however, and the time of trained therapists is especially costly. Existing rules and protocols about providing guidance can be programmed into the interventions themselves so as to be automatically safeguarded. Moreover, automated support through ECAs enables human support factors such as empathy to be delivered more effectively. Automated support could improve adherence rates of guided, and especially of unguided, web-based interventions and could thus improve their effectiveness.

While ECAs have been shown in many studies to be a feasible and acceptable technology in the domain of clinical psychology, very few applications have so far moved beyond the piloting phase. That is also the case for ECAs in iCBT contexts, where studies up to now have either been underpowered, have lacked control groups that set apart the ECA as the active ingredient, or have lacked depth in terms of underlying ECA technology. This study addresses these gaps in the literature in the following ways: (1) we designed a virtual coach that delivers automated support to iCBT for low mood, (2) we embedded it in an existing platform so that the platform can be used either with or without the ECA, and (3) we will estimate the effectiveness of a virtual coach in improving adherence and determine the parameters required for a proper RCT sample size calculation. Despite the technical limitations that come with embedding an ECA in an existing intervention platform, our virtual coach satisfies the criteria for an ECA—graphical embodiment, communicating with the user, and applying a form of reasoning—and conforms to recommendations from the literature. As a result, this study could represent a significant step in bridging the gap between guided and unguided iCBT interventions.

## Trial status

### Protocol version

Version 1.0, 25 October 2019

### Recruitment

Start date: 1 January 2021

End date: 30 June 2021

## Data Availability

Anonymized data used for statistical analysis will be published with the results paper and archived in a public data repository. Study materials such as the intervention content and informed consent form will be shared with other researchers upon reasonable request.
